## Abstract

The swallowing function is often compromised immediately after general anesthesia owing to the effects of anesthetic agents. Consequently, pharyngeal residue may accumulate, which increases the risk of aspiration during the perioperative period. Therefore, we designed a single-arm, open-label study, developing an artificial intelligence (AI)-based acoustic analyzer for quantifying pharyngeal residues and evaluating its efficacy. A sample of 30 patients aged ≥18 years scheduled for jaw deformity surgery will be enrolled in this study. Immediately after tracheal tube extubation, adventitious sounds from pharyngeal residues, such as saliva and blood, will be measured and quantified using an AI acoustic analysis system. Subsequently, the residual pharyngeal fluid will be suctioned and quantified by measuring the change in container weight before and after collection. The primary outcome measure will be the comparison of adventitious sounds before and after pharyngeal suction, and the secondary outcome will be the correlation between pharyngeal residue volume and adventitious sounds. The results of this study are expected to be drawn by 2025 upon its completion. This study will demonstrate the feasibility of AI-based acoustic monitoring for quantifying increased pharyngeal residues during perioperative management. This approach has the potential to reduce the risk of postoperative aspiration with a simple and inexpensive method.

## Introduction

Swallowing dysfunction is frequently observed immediately after general anesthesia because of the residual effects of anesthetics, narcotics, and postoperative pain [1]. Consequently, pharyngeal residues often increase. Meta-analyses of the American Society of Anesthesiology Closed Claims database indicate a rising trend in perioperative complications, particularly aspiration following extubation [2]. Considering that this tendency persists despite advancements in anesthetic agents, muscle relaxants, airway management devices, and monitoring instruments [3], the current airway management protocols and monitoring methods may not be adequate to prevent postoperative aspiration. We hypothesized that detecting an increase in pharyngeal residue (e.g., saliva or blood) would alert healthcare professionals to an elevated risk of aspiration, enabling timely interventions such as suctioning. Therefore, we developed an electronic auscultation system capable of detecting such pharyngeal residues [4,5].　

In a previous investigation conducted using a prototype system, the adventitious sound index increased when 5 cc of fluid was instilled into the oral cavity of 60 patients undergoing monitored anesthesia care [6], and this trend was more pronounced in patients with obesity [7]. Nevertheless, as the actual pharyngeal residue was not verified during the intervention, the correlation between the pharyngeal residue and adventitious sound index has not been conclusively demonstrated [6]. Therefore, we designed a single-arm comparative trial protocol to clarify the correlation between the newly developed adventitious sound index and pharyngeal residues and validate the use of the adventitious sound index to observe increases in pharyngeal residues as an early indicator of aspiration.

## Materials and methods

Ethical considerations

This study was approved by the Hiroshima University Certified Review Board (approval number: E2024-0025) and registered at UMIN (UMIN000055020). Written informed consent will be obtained from all patients or their guardians.

Study design

The first draft of the study protocol was finalized on April 18, 2024, following the Standard Protocol Items: Recommendations for Interventional Trials (SPIRIT) Reporting Guidelines. Table 1 presents the primary and secondary objectives of this study. The primary endpoint of this study is to identify the association between pharyngeal residue levels and the adventitious sound index. In addition, we aim to clarify the feasibility of monitoring aspiration risk using the newly developed AI-based adventitious sound analysis system. The secondary endpoints are to verify the correlation between the pharyngeal residue volume and adventitious sounds. 

**Table 1 TAB1:** Primary and secondary endpoint.

Endpoints	Details
Primary	Acoustic sensors will placed on the neck and chest to compare the adventitious sound index before and after aspiration of pharyngeal residues at each location.
Secondary	(1) Correlation between the mass of pharyngeal residue and the adventitious sound index. (2) Acoustic sensors will be placed on the neck and chest to compare the adventitious sound index before aspiration of pharyngeal residues at each location.

Sample size calculation 

A single-arm, pre-post comparison study was previously conducted among 19 patients with obesity who underwent anesthesia monitoring using an acoustic monitoring device. The adventitious sound index was measured before and after intraoral water injection during monitored anesthesia. The mean ± standard deviation of the indeterminate sound INDEX before and after water injection was 0.0679 ± 0.056 and 0.1415 ± 0.111, respectively. Based on these measurements, an effect size of 0.58 was calculated using G*Power software (version 3.1.9.6, Heinrich-Heine-Universität Düsseldorf, Düsseldorf, Germany). Using a two-sided test at a 5% significance level, 26 participants are required to maintain 80% statistical power. After accounting for an anticipated dropout rate of approximately 10%, a final sample of 30 participants is deemed necessary.

Inclusion and exclusion criteria

We will recruit patients who are scheduled to undergo osteotomy of the upper and lower jaw for osteodeformity. The detailed inclusion and exclusion criteria are presented in Figure 1.

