**Figure 2 FIG2:**
[figure not shown]
Containers for collecting residual pharyngeal fluid. Red arrow: Connect this end to the suction device.

Data collection

Two anesthetists will confirm the clinical evaluation and anesthetic records, and the following data will be recorded: height, weight, sex, degree of obesity, presence of respiratory disease, presence and degree of sleep apnea, Cormack-Lehane grading, presence of dysphagia, history of head and neck surgery, and presence of serious allergies. Six anesthesiologists will collect the auscultation data, and the presence or absence of profuse nasal bleeding and compliance with monitoring procedures will be recorded. 

The auscultation data will be stored as comma-separated value (CSV) files generated at one-second intervals from AI-based analyses, and these data will be cross-referenced with the corresponding WAV audio files. Within the three-minute recording periods before and after pharyngeal suctioning, auscultation segments with minimal noise and patient movement will be identified. Among these segments, we will determine the segments intended as reference intervals for the comparison of adventitious sound indices. If sensor detachment, application freezing, or noncompliance with sampling procedures for pharyngeal residue is observed during data acquisition, data collection is discontinued.

Statistical analysis

The 30-second mean values of the adventitious sound index measured before and after suction will be calculated, and a paired t-test will be performed for each of the three categories of the index. To determine the superior monitoring location, the index values obtained before suction will be subjected to analysis of variance for each type of index at both the cervical and thoracic monitoring sites. Statistical significance will be set to p < 0.05. significant. All statistical analyses will be conducted using SPSS v. 25 for Mac (IBM Corp., Armonk, NY).

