## Discussion

In our previous single-cohort intervention study, we demonstrated that the adventitious sound index responded significantly when water was instilled into the oral cavities of patients managed under monitored anesthesia care. However, this previous study did not confirm whether the instilled water actually accumulated in the pharynx [6]. Therefore, using the present protocol, we plan to clarify the correlation between the adventitious sound index and pharyngeal residue by collecting and weighing the pharyngeal residue immediately after awakening from general anesthesia using a video laryngoscope. We will also compare the adventitious sound index before and after this procedure. Using this approach, we expect to elucidate the correlation between pharyngeal residues and adventitious sound indices.

In our previous studies, the sensors for respiratory sound monitoring devices were positioned in the peripharyngeal region [6,7], and increases in the adventitious sound index observed at this site were presumed to result from airflow alterations synchronized with inspiration driven by the pharyngeal residue. However, adventitious sounds have also been identified as arising from bubbling sounds related to intratracheal secretions [8]. Consequently, we could not exclude that the increased adventitious sound index detected in the neck region may have been produced by intratracheal secretions rather than pharyngeal residues. In the current study, we plan to place sensors on both the neck and chest. By comparing the adventitious sound indices at these two anatomical sites, we anticipate that the origin of adventitious sounds could be precisely identified.

Our study group reported that the respiratory sound monitoring system used in this study can quantify the level of adventitious sounds generated in the pharyngeal region by the infusion of water into the oral cavity [9-11]. Furthermore, it has been reported that the adventitious sounds index utilized by this AI system demonstrates approximately 80% sensitivity and specificity relative to physicians’ auscultatory assessments [4]. The adventitious sounds index is calculated at a rate of one frame per 12 milliseconds, enabling real-time and multi-channel monitoring of these sounds. It is anticipated that this system could be widely utilized for aspiration risk monitoring in various clinical situations. 

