In another study, pharyngeal residue was evaluated by attaching an acoustic sensor to the neck (paralaryngeal region) to measure adventitious sounds [12,13]. Although paralaryngeal auscultation with a traditional analog stethoscope is commonly employed in clinical practice to detect pharyngeal residue, it is necessary to exclude or consider the possible influence of adventitious sounds from the lungs when performing automatic respiratory sound analysis [14,15]. Therefore, in the present study, auscultation of the chest (at the upper sternal border) will also be conducted, and the magnitudes of the adventitious sound indices obtained from both sites will be compared. Lung diseases are added to the exclusion criteria, and the influence of adventitious sounds transmitted from the lungs is eliminated by performing endotracheal suctioning before extubation. By doing so, we can specifically infer the adventitious sounds arising solely from pharyngeal residue.

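### Table 1 makes neck and chest jointly primary with no lead site, so the planned tests cannot show that the change after suction is specific to the neck

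*Protocol article*

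**What the plan says.** The protocol article gives the chest sensor three roles.

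- **Primary efficacy site.** Table 1, primary endpoint: sensors go on both neck and chest to "compare the adventitious sound index before and after aspiration of pharyngeal residues at each location". Neck and chest stand on equal terms.
- **Reference for sound from elsewhere.** The Discussion says of the earlier neck-only work that "we could not exclude that the increased adventitious sound index detected in the neck region may have been produced by intratracheal secretions". It then adds the chest and states: "By comparing the adventitious sound indices at these two anatomical sites, we anticipate that the origin of adventitious sounds could be precisely identified". Later in the Discussion, before chest auscultation is introduced, it says of automatic analysis that "it is necessary to exclude or consider the possible influence of adventitious sounds from the lungs".
- **Candidate monitoring site.** The Statistical analysis section begins its between-site analysis with "To determine the superior monitoring location" and applies analysis of variance to pre-suction values. This matches secondary endpoint (2) in Table 1, which is to "compare the adventitious sound index before aspiration of pharyngeal residues at each location".

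The before/after analysis is a paired t-test for each of three index categories. That sentence names no site; Table 1 supplies the two sites. The article gives no success criterion and does not say what a before/after change at the chest would mean.

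**The concern.** The roles call for different readings of the same result. If the chest is an efficacy site, a fall there after suction supports the index. If it is a reference site, a fall there similar to that at the neck leaves the source of the sound open. The article does not say which reading applies to the primary analysis.

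This matters because the study has one arm and a before/after design. No group shows what the index does over the same minutes without suction. The Discussion itself lists swallowing, coughing, vocalisation and room noise as things that alter the residue or the index. The chest sensor is the only concurrent comparator within the patient. If it enters the primary endpoint as a second site to be tested on its own, that comparison is not used, although the Discussion concludes that the design allows sound from the pharynx alone to be inferred.

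**Working it through.** **1. What the planned tests address.** Let L_N and L_C be the pre-suction index levels at neck and chest, and D_N and D_C the falls after suction.

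| Planned analysis | Hypothesis tested |
|---|---|
| Paired t-test, neck | D_N = 0 |
| Paired t-test, chest | D_C = 0 |
| Analysis of variance, pre-suction values | L_N = L_C |
| Not planned | D_N = D_C |

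Specificity of the change concerns the last row. The pre-suction comparison does not supply it, since two sites can differ in level and change equally, or agree in level and change differently. A significant neck test beside a non-significant chest test does not supply it either, because that is not a test of the difference. The neck test also has the same power whether the chest falls by nothing or by as much as the neck, so it cannot separate those two cases.

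**2. The plan's own sample size.** Inputs from the Sample size calculation: effect size 0.58, two-sided 5%, 80% power. For a paired t-test with n = 26 the noncentrality is 0.58 × √26 = 2.96 on 25 df. Power is 81.1%, and 26 is the smallest n that reaches 80%. Dropout: 26 / 0.90 = 28.9, so 29, against the stated 30 for a rate of about 10%. The figure reproduces. It covers one paired test. The paragraph does not name the sensor site, but the Discussion places the sensors of the group's earlier studies in the peripharyngeal region. No chest data are given.

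**3. Neck alone as primary.** For one index category the calculation is unchanged: 26, or 30 with dropout.

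**4. The neck-minus-chest change.** Assume equal SDs of change at the two sites, a neck effect of 0.58, a chest fall equal to a fraction f of the neck fall, and a correlation r between the two changes. The article gives neither f nor r, so a range is shown. The standardised effect is

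d = 0.58 × (1 − f) / √(2(1 − r))

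| r | d, f = 0 | Power, n = 26 | n for 80% | d, f = 0.25 | Power, n = 26 | n for 80% |
|---|---|---|---|---|---|---|
| 0 | 0.410 | 52% | 49 | 0.308 | 33% | 85 |
| 0.3 | 0.490 | 67% | 35 | 0.368 | 44% | 61 |
| 0.5 | 0.580 | 81% | 26 | 0.435 | 57% | 44 |
| 0.8 | 0.917 | 99% | 12 | 0.688 | 92% | 19 |

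**5. Precision as an estimate.** In units of the SD of change at one site, the 95% CI half-width at n = 26 is 2.06 × √(2(1 − r)) / √26, which is 0.57, 0.48 and 0.40 for r = 0, 0.3 and 0.5. Against a difference of 0.58 (no chest change), the interval is informative but wide at low correlation.

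**The case against.** The strongest reply is that measuring one site for two purposes is not a contradiction. Assessing both sites is a stated aim, and a reference reading needs the same chest measurements. The origin check is secondary endpoint (2). Secondary endpoint (1) links the index to weighed residue, so the case does not rest on the before/after test alone. Lung disease is excluded, endotracheal suction precedes extubation, and quiet segments are selected. Rules for reading result patterns may also sit in a full protocol or SAP that is not shown.

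Much of this stands, and it limits the point. A reader might infer that a chest fall counts as success under the plan while the protocol regards it as contamination. The article supports neither half. It states no either-site success rule. Its stated worry is that tracheal or lung sound raises the neck index; it does not call a fall at the chest contamination. Since suction is aimed at the pharynx, a chest fall could be transmitted pharyngeal sound. A reader might also put the probability of a significant chest result at 81%, but that only moves the planning effect of 0.58 to a site with no data.

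The reply does not remove the core. Which sites are primary is fixed in Table 1 itself and is not left to another document. Secondary endpoint (2) compares levels before suction and says nothing about change. The residue correlation does not compare the sites' changes either. The measures against lung sound reduce the problem, but the same part of the Discussion still adds the chest sensor because of it.

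**Conclusion.** The point holds as a weakness in how the primary endpoint is defined. Neck and chest are jointly primary with no lead site, the chest's reference role is not carried into the primary analysis, and no planned test compares the change at the two sites. As written, the analysis cannot show that the change after suction is specific to the neck. The wording leaves room to read a chest-only or equal fall as support, but does not say that it would be so read.

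The stated sample size is not shown to be wrong; it stands for one neck comparison in one index category. The figures for the difference in change rest on assumed correlations, equal SDs and an assumed chest change. The change is worth making before the data are analysed, and it does not put the study in doubt.

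**What to change.** - **Table 1, primary endpoint:** name the neck, the region used in the earlier studies, as the primary site for the before/after comparison.
- **Table 1, secondary endpoints:** list the chest before/after comparison as secondary, labelled as the reference site, and add the within-patient difference in change (neck minus chest) as a key secondary estimate with a 95% CI.
- **Statistical analysis:** name the site in the paired t-test sentence, and state the reading in advance. A larger fall at the neck supports pharyngeal origin. Similar falls at both sites are inconclusive about origin, since they could reflect transmitted pharyngeal sound or a non-pharyngeal change. A chest-only fall does not meet the primary endpoint.

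The cost is wording plus one paired contrast on data already to be collected. Two things are given up or limited: a chest-only result can no longer be claimed as primary, and the difference may be imprecise, more so if the chest also falls. For that reason it should be reported as an estimate and not made a powered primary test.

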**Figure 1 FIG1:**
[figure not shown]
Schema of the study protocol.

Table 2 shows the SPIRIT schedule for patient enrollment, interventions, and assessments.

**Table 2 TAB2:** SPIRIT schedule of enrollment, interventions, and assessments. Table 2 shows the SPIRIT schedule for patient enrollment, interventions, and assessments.

Study period	Pre-Enrolment	Enrolment	Post-Enrolment	Close-out
Time point	-1 day	0 day	+1 day	
Enrolment	X			
Eligibility screen	X			
Informed consent	X			
Respiratory sound monitoring		X		X
Collection of pharyngeal residual fluid		X		X
Residual fluid in the pharynx		X		X
Respiratory sound analysis		X		X

Procedure

Propofol, remifentanil or fentanyl, and rocuronium will be used for general anesthesia. Intraoperative monitoring includes electrocardiography, oxygen saturation measurements, capnography, bladder temperature measurements, electroencephalography, and neuromuscular function measurements. Extubation during emergence will be performed once the train-of-four (TOF) ratio and the Entropy index (GE Healthcare’s Brain Monitoring System) have recovered to at least 90% and it is confirmed that the patient can open their eyes, open their mouth, and elevate their tongue.

The study procedure is illustrated in Figure 1. Immediately after extubation, the respiratory sound monitoring device will be attached to the skin of the neck (paralaryngeal region) and chest (beneath the sternal notch) using an adhesive tape (TransporeTM, White, 3M, USA). Subsequently, respiratory sound sampling will be initiated. After three minutes of sampling, the residual pharyngeal fluid will be suctioned using a McGrathTM MAC videolaryngoscope (Aircraft Medical Ltd., Edinburgh, UK), and an additional three minutes of respiratory sound recording will be performed. The residual pharyngeal fluid will be aspirated into a container (Triple Seal CapTM, AGC Techno Glass Co., Shizuoka, Japan; Figure 2), and after suctioning, the residual material inside the suction tube will also be flushed using 20 mL of normal saline. The weight of the pharyngeal residual substance will be measured as the change in the weight of the container before and after fluid collection.

**Figure 2 FIG2:**
[figure not shown]
Containers for collecting residual pharyngeal fluid. Red arrow: Connect this end to the suction device.

Data collection

Two anesthetists will confirm the clinical evaluation and anesthetic records, and the following data will be recorded: height, weight, sex, degree of obesity, presence of respiratory disease, presence and degree of sleep apnea, Cormack-Lehane grading, presence of dysphagia, history of head and neck surgery, and presence of serious allergies. Six anesthesiologists will collect the auscultation data, and the presence or absence of profuse nasal bleeding and compliance with monitoring procedures will be recorded. 

The auscultation data will be stored as comma-separated value (CSV) files generated at one-second intervals from AI-based analyses, and these data will be cross-referenced with the corresponding WAV audio files. Within the three-minute recording periods before and after pharyngeal suctioning, auscultation segments with minimal noise and patient movement will be identified. Among these segments, we will determine the segments intended as reference intervals for the comparison of adventitious sound indices. If sensor detachment, application freezing, or noncompliance with sampling procedures for pharyngeal residue is observed during data acquisition, data collection is discontinued.

Statistical analysis

The 30-second mean values of the adventitious sound index measured before and after suction will be calculated, and a paired t-test will be performed for each of the three categories of the index. To determine the superior monitoring location, the index values obtained before suction will be subjected to analysis of variance for each type of index at both the cervical and thoracic monitoring sites. Statistical significance will be set to p < 0.05. significant. All statistical analyses will be conducted using SPSS v. 25 for Mac (IBM Corp., Armonk, NY).

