The acoustic sensor employed in the process is a cost-effective displacement-detection vibration sensor. By clarifying the sensor installation requirements necessary for identifying pharyngeal residues through acoustic monitoring, a novel evaluation method for quantifying the perioperative aspiration risk may be established, it is envisaged that the device will establish a widely applicable pharyngeal residue assessment index. Nevertheless, several limitations are identified in the method used to validate this research. First, the collected liquid residue contains various substances, including blood, saliva, and mucus. Although changes in weight serve only as a quantitative indicator, it remains unclear which types of fluid pose the aspiration risk. Furthermore, the findings may not be generalizable to surgeries other than those involving the head and neck. Second, the evaluation of pharyngeal residue using the adventitious sounds index is subject to confounding factors, including obesity, upper airway obstruction such as sleep apnea, and underlying conditions like tonsillar hypertrophy. In particular, a correlation has been reported between obesity, body mass index (BMI), and the adventitious sounds index [7]. These confounding factors will be documented, and a multivariate analysis will be performed. Third, the inability to restrict the patient’s swallowing has been identified as a concern. When the pharyngeal residue is swallowed by the patient, the amount of residue is inevitably reduced. Fourth, it should be noted that the adventitious sounds index can be increased by environmental noise, as well as by the patient’s own vocalization or coughing.

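### The final choice of the segments compared in the primary analysis has no stated rule that treats the recordings before and after suction alike

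*Protocol article*

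**What the plan says.** Table 1 of the protocol article makes the comparison of the index before and after suction the primary endpoint, at neck and chest. Under Procedure, each period is recorded for three minutes: "After three minutes of sampling, the residual pharyngeal fluid will be suctioned", and a second three-minute recording follows.

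Under Data collection, the software's one-second index values are stored and "these data will be cross-referenced with the corresponding WAV audio files". Segments are then selected in two steps:

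1. "Within the three-minute recording periods before and after pharyngeal suctioning, auscultation segments with minimal noise and patient movement will be identified". This gives a qualitative criterion, in one sentence that covers both periods, without a threshold.
2. "Among these segments, we will determine the segments intended as reference intervals for the comparison of adventitious sound indices". This gives no criterion.

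Statistical analysis then states: "The 30-second mean values of the adventitious sound index measured before and after suction will be calculated, and a paired t-test will be performed".

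Two further statements bear on this. The Abstract says "we designed a single-arm, open-label study". The Discussion, listing limitations, says "the adventitious sounds index can be increased by environmental noise, as well as by the patient’s own vocalization or coughing".

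**The concern.** A three-minute recording holds up to 180/30 = 6 non-overlapping 30-second windows, so more than one acceptable window per period is likely in at least some patients. The plan does not say which of them is analysed. The team expects the index to be higher before suction than after it. What is set aside as noise also moves the outcome, because noise raises the index. If a loud window is kept before suction and a comparable one is passed over after suction, the paired difference shifts in the expected direction with no change in residue.

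The trial has a single arm, so no control group would share and cancel such a shift. An analysis confined to the chosen segments could not reveal it either. At stake are the size of the primary estimate and the 5% error rate of its test.

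**Working it through.** **The plan's own figure.** The means before and after water injection in the earlier study were 0.0679 and 0.1415, a difference of 0.0736. With the stated effect size of 0.58, the implied SD of the paired difference is 0.0736/0.58 = 0.127. An exact paired t-test (noncentral t, two-sided 5%) has power 79.5% with 25 patients and 81.1% with 26, so the stated 26 is reproduced. Of 30 enrolled, 10% dropout leaves 30 × 0.9 = 27, the number used below.

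**Assumptions, since the documents give no within-recording variance.** There is no true change. The SD of the difference between two single 30-second windows is 0.127. A share w of that variance comes from window-to-window variation within a period. The SD of one window around its period level is then s = 0.127 × √(w/2). Windows are independent unless stated otherwise.

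**Expected spurious fall.** The higher of two independent normal values lies s/√π above its mean on average, and the lower lies s/√π below. Taking the higher before and the lower after, in a fraction f of patients, gives

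fall = f × 2s/√π.

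- w = 25%, f = 1: s = 0.127 × √0.125 = 0.0449; fall = 2 × 0.0449/1.772 = 0.051, which is 69% of 0.0736.
- w = 5%, f = 0.5: s = 0.127 × √0.025 = 0.0201; fall = 0.5 × 2 × 0.0201/1.772 = 0.011, which is 15% of 0.0736.
- w = 25%, f = 1, windows correlated at 0.7: the gain shrinks by √(1 − 0.7) = 0.548; fall = 0.051 × 0.548 = 0.028, which is 38% of 0.0736.

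**False positives, by simulation (n = 27, two-sided 5%, two candidate windows per side).**

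| Segment share w | One fifth of patients | Half | All |
|---|---|---|---|
| 5% | 5% | 7% | about 14% |
| 10% | 6% | 9% | 25% |
| 25% | 7% | 17% | 55% |

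With windows correlated at 0.7 and w = 25%, the rate is about 20% when all patients are affected and about 9% when half are.

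**Same rule in both periods.** Taking the lowest window before and the lowest window after (w = 25%) gives a mean difference of zero and a type I error of about 5%, whether there are two candidates or six. A fixed window on each side also gives about 5%. The error rate therefore rises only when the two periods are treated differently.

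**The case against.** Much of the opposing case stands.

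- **Excluding noisy stretches is right.** The index responds to noise and coughing, so a quietness criterion is needed, and the article applies it to both periods in one sentence. The choice is not free.
- **Masking is not ruled out.** A reader might infer that segments will be picked by someone who knows the period and sees the index. The article does not say so. It describes no masking and calls the study open-label, and its cross-referencing sentence may mean only that index rows are matched to audio.
- **The paired t-test does not need segments chosen independently of their index values.** The same-rule result shows this. The need is for like treatment of the two periods.
- **Much larger error rates need stronger assumptions.** Best of six windows, in opposite directions in every patient, gives nearly 100% false positives at w = 25%. That requires every window to pass the quietness criterion in patients just extubated. At w = 5% the same extreme gives a little over 50%.
- **This is a condensed article.** A numeric noise limit or a reader manual may well sit in the full protocol or SAP, and their absence here is no fault.

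What remains is the text itself. The article does describe how the primary data are produced, and it gives the last step as a decision by the team, without a rule and without a requirement that the two sides be handled alike.

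**Conclusion.** The point holds in this form: the final selection of the segments behind the primary comparison is left open, and choosing differently before and after suction can create a fall that is not there. Under no true effect, with two candidates per side and 27 patients, false positives are about 7% at a 5% segment share with half the patients affected, and about 55% at a 25% share with all affected. The latter drops to about 20% if segments correlate at 0.7. The variance share, the number of candidates, the fraction of patients and the correlation are all assumptions.

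A reader might conclude that the trial will yield a biased result, or that its error rate is above half. The documents do not support that. They neither plan opposite selection nor allow its size to be estimated. This is a change that should be made, and it does not invalidate the design.

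**What to change.** Before any recording is read, state the following:

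1. Artefacts are marked from audio files coded so that the reader does not know the period, with the index values withheld.
2. A script then applies one identical rule to both periods. Examples are the mean index over all artefact-free seconds, or the same pre-specified 30-second rule on each side.
3. The mean over the full three minutes, before and after, is reported as a sensitivity analysis. It involves no selection, but it includes the artefacts, so it checks the primary result and does not replace it.

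A mirrored rule, such as the last clean 30 seconds before suction and the first clean 30 seconds after it, is less suitable. It treats the periods differently and puts the second window directly after videolaryngoscopy and suction.

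The cost is coding the file names and a short script. With a fixed common rule the simulated type I error is about 5%, and the sample size stays at 26 evaluable and 30 enrolled.
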